## Abstract

**Background:**

Couples-based HIV counseling and testing (CHCT) is a proven strategy to reduce the risk of HIV transmission between partners, but uptake of CHCT is low. We describe the study design of a randomized controlled trial (RCT) aimed to increase participation in CHCT and reduce sexual risk behavior for HIV among heterosexual couples in rural KwaZulu-Natal, South Africa. We hypothesize that the rate of participation in CHCT will be higher and sexual risk behavior will be lower in the intervention group as compared to the control.

**Methods/design:**

Heterosexual couples (N = 350 couples, 700 individuals) are being recruited to participate in a randomized trial of a couples-based intervention comprising two group sessions (one mixed gender, one single gender) and four couples’ counseling sessions. Couples must have been in a relationship together for at least 6 months. Quantitative assessments are conducted via mobile phones by gender-matched interviewers at baseline, 3, 6, and 9 months post-randomization. Intervention content is aimed to improve relationship dynamics, and includes communication skills and setting goals regarding CHCT.

**Discussion:**

The Uthando Lwethu (‘our love’) intervention is the first couples-based intervention to have CHCT as its outcome. We are also targeting reductions in unprotected sex. CHCT necessitates the testing and mutual disclosure of both partners, conditions that are essential for improving subsequent outcomes such as disclosure of HIV status, sexual risk reduction, and improving treatment outcomes. Thus, improving rates of CHCT has the potential to improve health outcomes for heterosexual couples in a rural area of South Africa that is highly impacted by HIV. The results of our ongoing clinical trial will provide much needed information regarding whether a relationship-focused approach is effective in increasing rates of participation in CHCT. Our intervention represents an attempt to move away from individual-level conceptualizations, to a more integrated approach for HIV prevention.

**Trial registration:**

Study Name: Couples in Context: An RCT of a Couples-based HIV Prevention Intervention

ClinicalTrials.gov identifier: NCT01953133.

South African clinical trial registration number: DOH-27-0212-3937

## Background

The estimated prevalence of HIV in South Africa is 17.9% among 15- to 49-year-olds and 39.5% among female antenatal clinic attendees in KwaZulu-Natal [1], indicating a continuing need for effective HIV prevention. Further, recent studies in sub-Saharan Africa found 60% to 94% of new HIV infections occur within marriage or co-habiting heterosexual partnerships [2]. South Africa has low rates of marriage compared to many other sub-Saharan African countries, and also has a high level of partner non-cohabitation in non-marital and marital couples, often due to migration by both partners [3]. Recent national HIV testing campaigns in South Africa have improved rates of individual testing [4], but in rural KwaZulu-Natal the percent of men knowing their HIV status (55%) still lags behind women (83%) [5]. Project Accept, a community-level randomized controlled trial (RCT), found high rates of multiple partnerships (32%) among men aged 18 to 32 years in rural South Africa [6]. In contrast, longitudinal population-based data from another area of rural KwaZulu-Natal suggests that the proportion of men having multiple or concurrent sexual partnerships has been declining in recent years, to approximately 12% and 6% of men aged 17 to 54 years reporting multiple and concurrent sexual partners, respectively, in 2011 [7]. Other challenges concerning HIV status disclosure also remain. For example, in a cohort of HIV-positive individuals in rural KwaZulu-Natal, many do not know their partner’s HIV status and do not disclose their own positive status [8]. Since 1992, couples-based HIV counseling and testing (CHCT) is a proven strategy to reduce the risk of HIV transmission between partners due to mutual disclosure of HIV status [9]. However, uptake of CHCT is low [10-12]. Reasons include: a lack of environments that are welcoming to couples and men; the need for both partners to be willing to participate, which could be impacted by the presence of intimate partner violence, or unwillingness to disclose HIV serostatus; and a lack of community mobilization and support for CHCT [10]. These circumstances signal the need for HIV prevention interventions that: 1) target couples; 2) increase uptake of CHCT; and 3) examine the role of relationship factors on testing and sexual behaviors.

Several benefits of CHCT were identified by the World Health Organization (WHO) working group on CHCT [13]. First, CHCT provides a springboard for early antiretroviral therapy (ART) initiation, which has been found to be highly efficacious for reducing morbidity and mortality and in reducing HIV transmission within serodiscordant partnerships [14]. Second, CHCT provides a foundation for both primary and secondary HIV prevention. For example, recent evidence points towards dramatic decreases in sexual risk following knowledge of serodiscordance via CHCT. Rosenberg and colleagues [15] reported that unprotected intercourse decreased from 71% to 8% in 1 month following knowledge of serodiscordance via CHCT among couples who participated in the Partners in Prevention HSV/HIV Transmission Study in three sites in South Africa. The authors suggested that it is the awareness of their discordant serostatus as a couple which is the driver of the reduction in sexual risk, as opposed to an individual level of knowledge of HIV-positive serostatus. CHCT could also impact sexual risk behavior with outside partners, thereby reducing HIV transmission to secondary partners. Third, CHCT has the potential to improve the success of safer conception strategies, an approach that is enhanced by the increasing availability of pre-exposure prophylaxis (PReP) and early ART initiation. Similarly, CHCT has the potential to improve uptake, retention, and adherence to family planning, prevention of mother-to-child transmission (PMTCT), and ART-focused interventions. Finally, the WHO also identified increased emotional support and positive relationship outcomes as potential benefits for couples that participate in CHCT. However, even given these potential benefits, no prior intervention study has had CHCT as its outcome.

Prime among its benefits is that CHCT requires mutual disclosure. Given this aspect of the procedure, consistent findings of effectiveness of CHCT in reducing sexual risk are not surprising. This mutual knowledge provides a solid foundation from which to make mutual decisions about sexual behavior with each other, and provides an opening for discussions regarding HIV. However, couples must be psychologically ready to enter into the testing process together [16], which can be more threatening than finding out one’s own status. Testing as a couple can result in knowledge that could threaten a relationship, and escalate fear of results in terms of one’s own health, one’s partner’s health, and the stability of a relationship [17]. From a relationship-based perspective, it is understandable why rates for CHCT are low; avoiding activities that may threaten a relationship may be protective of relationships.

CHCT is a highly effective strategy towards preventing new HIV infections; but motivations to participate in couples-based testing are relationship-focused, which can complicate the decision-making process. Partners want to establish trust, demonstrate commitment to each other, and know their HIV status prior to embarking on future decisions such as having children together, or getting married [18]. Evidence from our research group [19] and others [20-26] indicates that a comprehensive approach that includes such components as education and skills-building in couples’ communication is necessary to successfully tackle the myriad of issues facing heterosexual couples in sub-Saharan Africa.

While the benefits of CHCT are clear, gaps remain in our knowledge regarding couples and HIV prevention. When examining prior investigations of couples-based interventions, several issues emerge. First, couples-based interventions have typically adapted individually-focused interventions for couples [27,28]. Second, most couples-based HIV prevention interventions have included only couples where both partners know their own and their partner’s HIV status when evaluating sexual risk behavior outcomes [29]. However, men often use their female partner’s status as a proxy for their own HIV status, without ever having been tested themselves [30]. Often CHCT is, indeed, the intervention itself [9,31,32], and the goals of the intervention have been to determine the effectiveness of participating in CHCT as a risk reduction strategy. Third, other sexual behavior risk factors are important to consider, including the presence and frequency of unprotected sex with both primary and outside concurrent partners [33,34]. Finally, relationship factors have been shown to be associated with condom use, such that longer-term relationships often result in low or inconsistent condom use [35-37]. For example, Vamos and colleagues found, from their couples-based intervention in Zambia, that couples who were more positive about their relationship engaged in significantly higher condom use. These findings indicate that interventions that improve and enhance couples’ relationship dynamics may also have potential to exert change on behavioral outcomes that can improve HIV prevention efforts [38].

Prior couples-based approaches to HIV prevention have employed individually-focused theoretical orientations, thereby neglecting the influence that partners play in decisions around HIV, both its prevention and potential transmission. Interdependence theory [39,40] provides a framework for understanding relationship dynamics and emotional responses in the context of intimate relationships. It has been applied in studies of couples to explore how relationship dynamics (for example, commitment) influence relationship outcomes such as longevity, divorce, and infidelity [41,42]. Lewis and colleagues [43] extended the interdependence theory to examine both the initiation and maintenance of health-enhancing behaviors. Their model proposes that engaging in health-enhancing behaviors is the end result of relationship dynamics, such as relationship satisfaction and commitment, which are essential predisposing factors for a ‘transformation of motivation’. This transformation produces a shift in partners from an individually-centered perspective to one that is more relationship-oriented. Once this shift occurred, a couple then engages in joint efforts and cooperative action to achieve or maintain positive outcomes. For example, both partners would choose to engage in less HIV risk with outside partners in order to lessen the chances of HIV transmission for both of them, as opposed to only one partner choosing to do so.

The Prevention and Relationship Enhancement Program (PREP) is one of the most studied couples-based relationship education interventions, aimed at improving relationship success. It has demonstrated long-term (2- and 5-year) positive effects on relationship outcomes (for example, relationship satisfaction) [44]. It is based on behavioral marital therapy (BMT [45]) that focuses on problem-solving skills for couples and communication skills. Long-term outcomes have also included lower levels of relationship conflict [44]. The areas focused on in PREP are closely aligned with the relationship factors emphasized in interdependence theory [46] (improving intimacy, commitment, and so on). In addition, PREP includes identification of specific relationship goals. Our intervention approach is therefore based upon a combination of the theoretical perspective of interdependence theory and empirical findings; we hypothesize that couples that have more intimacy, stronger commitment, and clearer communication about sexuality and HIV are more likely to test for HIV together.

In sum, understanding and intervening within the dyadic context of HIV risk in South Africa is a critical component of reducing new HIV infections. Further, prior interventions have not examined predictors of participating in couples-based testing, and most couples-based interventions have only included serodiscordant couples [9,47]. The Uthando Lwethu study represents an effort to address the gaps in our knowledge by testing the efficacy of a couples-based behavioral intervention in increasing uptake of CHCT and reducing sexual risk behavior for HIV among heterosexual couples living in rural KwaZulu-Natal, South Africa. As knowledge of status is a gateway to HIV treatment and sexual risk reduction opportunities, increasing testing for HIV within partnerships is a high-impact outcome.

## Methods/design

### Objectives

Uthando Lwethu is a couples-based RCT to test the efficacy of providing relationship-based counseling (for example, targeting communication skills, improving commitment, and intimacy) to increase the rates of CHCT among a population of heterosexual couples in rural KwaZulu-Natal, South Africa. A second primary outcome is reduction of sexual risk behavior (that is, condom use with primary partner in the last 3 months). We hypothesize that by improving positive relationship dynamics among couples, their rates of CHCT will increase and the frequency of sexual risk will decrease.

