#### Data analysis

##### Primary outcome: CHCT

There are two primary outcomes for our trial: 1) participation in CHCT; and 2) sexual risk behavior. We hypothesize that:

1) The proportion of participants who participate in CHCT by 9-month follow-up will be higher in the intervention group than in the control group.

2) The time to participate in CHCT as a couple will be shorter in the intervention group relative to the control group.

Our initial analyses to address these hypotheses will follow an intention-to-treat (ITT) approach and will be unadjusted. To evaluate hypothesis 1, a chi-square test will be used to compare the proportion of couples that participate in CHCT in the intervention group with the proportion of couples in the control group who participate in CHCT. To evaluate hypothesis 2, we will construct Kaplan–Meier curves to display the two groups’ survival functions and use a log-rank test to compare the two groups’ survival times. Both groups are getting equal exposure and access to testing, beginning from the participation in the first group. Couples will be the unit of analysis for hypotheses 1 and 2. The analysis for hypothesis 1 does not account for when the testing actually occurred, but only examines differences between the intervention and control group at the time of final 9-month follow-up. The analysis for hypothesis 2 will allow us to conduct more nuanced comparisons as to the timing of testing, for example, subsequent to the baseline survey, first intervention group, or follow-up interviews. Thus, we will have our primary comparison of intervention versus comparison group HIV testing within the entire study period at the final follow-up as our primary outcome, and other analyses will further illuminate specific patterns of testing over the course of the study due to intervention participation or exposure. For example, it may be possible that the couples in the intervention condition may exhibit an average longer time to testing when compared to those in the control condition. We will be able to investigate any group differences in timing of testing via our proposed time-to-event analyses.

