#### Primary outcome: sexual behavior

In addition to CHCT, our intervention is designed to reduce sexual risk behavior for HIV. We hypothesize that:

1) During follow-up, intervention participants will report fewer acts of unprotected sexual intercourse with: a) primary sex partners; and b) outside sex partners, relative to participants in the control group.

2) During follow-up, intervention participants will report fewer concurrent outside (that is, secondary) sex partners relative to participants in the control group.

We will test longitudinal hypotheses using random effects models to examine changes in participant trajectories in sexual risk outcomes. These longitudinal analyses will treat the individual as the unit of analysis and will include an additional random intercept to account for within-couple response correlations. Initial analyses of sexual risk behavior will follow an ITT approach and include intervention group assignment, time of measurement, and an intervention group-by-time interaction term.

It is critical to optimize the accurate reporting of self-reported sexual risk behavior given its role as a primary outcome of our trial. To account for any possible bias, we have taken the following precautions: 1) we are using previously validated instruments; and 2) the assessment and intervention activities are conducted by different staff members. Thus, we do not expect any differential effects of social desirability reporting across arms of the study.

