#### Power analysis

With projected attrition of 20% due to break-ups and 10% due to other causes, we require 350 couples to be randomized in order to achieve the sample size target at 9 months of 245 couples at the final 9-month follow-up. As stated, our primary outcome is determined for only the final follow-up time point, and not for any other group differences at other intervention time points (for example, between first and second group session). The actual prevalence of couple HIV testing is unknown. Thus, for the proposed logistic regression analyses we computed the minimum detectable odds ratio assuming a low prevalence of couple HIV testing (10%) and a medium prevalence of couple HIV testing (30%). For these scenarios, the minimum detectable odds ratios were 2.85 and 2.18, respectively. This was calculated for 80% power. Given the resource-intensiveness of this study intervention, we believe a substantial odds ratio is needed to merit rollout of such an intervention on a public health scale. For time to couple HIV testing survival analyses, under the same assumptions, the minimum detectable hazard ratios are 2.70 and 1.77.

For our sexual behavior outcomes, the minimum detectable R^2^ values fall below 1% for this continuous variable, which is considered a ‘small’ effect size according to Cohen’s [62] criteria for the R^2^ statistic. We based our calculations on data which reported a base rate of 2.35 unprotected sex acts per 3 months (from the study by Genberg and colleagues [6]). We have 80% power to detect a reduction in the mean number of unprotected sex acts from a base rate of 2.35 to 2.04 or 2.12 depending upon the level of within-participant correlation of reported sex acts over time.

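### The second primary outcome, sexual risk behavior, is a different variable in the Objectives, the analysis section and the power section, and no one measure is singled out as decisive

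*Protocol article*

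**What the plan says.** The Data analysis section declares: "There are two primary outcomes for our trial: 1) participation in CHCT; and 2) sexual risk behavior". The second of these is then described in three places.

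- **Objectives:** "A second primary outcome is reduction of sexual risk behavior (that is, condom use with primary partner in the last 3 months". This fixes one behavior, one partner type and one recall window.
- **Primary outcome: sexual behavior:** the first hypothesis is that "intervention participants will report fewer acts of unprotected sexual intercourse with: a) primary sex partners; and b) outside sex partners", compared with control. The second is that "intervention participants will report fewer concurrent outside (that is, secondary) sex partners relative to participants in the control group". The random effects models will "include intervention group assignment, time of measurement, and an intervention group-by-time interaction term". The same section confirms the status of the outcome: "It is critical to optimize the accurate reporting of self-reported sexual risk behavior given its role as a primary outcome of our trial".
- **Power analysis:** "We have 80% power to detect a reduction in the mean number of unprotected sex acts from a base rate of 2.35 to 2.04", or to 2.12, depending on the within-participant correlation. It adds that "the minimum detectable R^2^ values fall below 1% for this continuous variable". One variable is meant, and its partner type is not given.

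For CHCT, by contrast, the Data analysis section singles out testing over the whole study period, assessed at the final follow-up, as the primary comparison. The Power analysis repeats that only the final time point counts.

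**The concern.** A primary outcome should be one variable that every section describes alike. Here the Objectives and the analysis section cannot both be followed: the first makes condom use the outcome, and the second does not list condom use among its hypotheses. Two of the three measures in the analysis section concern outside partners, whom the Objectives leave out of the definition.

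The difference is more than one of words. Let N be the number of sex acts and c the proportion protected. Unprotected acts are then U = N(1 − c). If N halves and c stays the same, U halves with no change in condom use. One measure would show a benefit and the other would not.

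At stake is which result decides the second primary outcome. While that is open, a report could give weight to one measure over another after the data are seen, and no section of the article would settle the matter.

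**Working it through.** **1. The sections side by side**

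| Section | Variable | Partner type | Recall or time | Number of measures |
|---|---|---|---|---|
| Objectives | Condom use | Primary | Last 3 months | 1 |
| Primary outcome: sexual behavior | Unprotected acts; number of concurrent partners | Primary and outside, separately; outside | During follow-up (3, 6 and 9 months) | 3 |
| Power analysis | Mean unprotected acts | Not stated | Per 3 months | 1 |

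No variable appears in all three rows. The nearest to common ground is unprotected acts with the primary partner. It has the partner type of the Objectives, is part (a) of the first hypothesis, and is the kind of count that was powered.

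**2. The plan's own figures**

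- *Sample size.* Attrition is 20% + 10% = 30%, and 245 / 0.70 = 350 couples. This reproduces exactly.
- *Sexual-risk power.* The step from 2.35 to 2.04 or 2.12 cannot be reproduced, because no standard deviation or correlation is given. It can be checked for plausibility under assumed Poisson variance, two-sided 5%, 80% power, 245 individuals per arm (245 couples × 2 partners / 2 arms), 3 visits and no within-couple correlation. Independent observations needed per arm are (μ1 + μ2)(1.960 + 0.842)² / (μ1 − μ2)².
  - To 2.04: 4.39 × 7.849 / 0.31² = 359. Available: 245 × 3 = 735. The design effect is 735 / 358.5 = 2.05, so the within-person correlation is (2.05 − 1) / 2 = 0.52.
  - To 2.12: 4.47 × 7.849 / 0.23² = 663. The design effect is 735 / 663.2 = 1.108, so the correlation is 0.05.

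The two stated figures are therefore not shown to be wrong. They cover one count variable, not three measures.

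**3. What three undifferentiated measures would do to the error rate**

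Inputs: three measures from the analysis section, each tested at two-sided 5% (assumed), with no true effect. Under independence, 1 − 0.95³ = 0.143. With correlated normal test statistics, by simulation with 1,000,000 draws per setting:

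| Pairwise correlation | At least one false positive | In the favorable direction only |
|---|---|---|
| 0 | 14.3% | 7.3% |
| 0.3 | 13.6% | 6.8% |
| 0.5 | 12.5% | 6.3% |
| 0.7 | 10.9% | 5.4% |
| One measure only | 5% | 2.5% |

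**The case against.** The strongest reply is that the mismatch is loose wording. The Objectives and part (a) of the first hypothesis agree on the primary partner. The Objectives go on to predict a lower frequency of sexual risk, which suits a count, and the Power analysis uses such a count. Condom use may be shorthand for unprotected acts. That is a fair reading and points to the natural repair. It does not explain the two outside-partner measures under a heading that says primary.

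A second reply is that model contrasts, hierarchies and multiplicity rules often sit in a statistical analysis plan, which is not at hand. That stands: a missing alpha rule alone would be no finding. But an analysis plan cannot follow both the Objectives and the analysis section, and for CHCT the article did fix the comparison.

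Four stronger inferences are tempting, and the article does not support them:

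- *That any one favorable measure counts as success.* No such rule is stated, and the separate hypotheses are not each labeled primary; only the section heading and text apply that label to sexual behavior.
- *That the power section spends 5% on each outcome.* No alpha is given. The CHCT odds ratios fit two-sided 5%: with continuity correction they need 125 and 122 couples per arm against 122.5 available. That is an inference, and for CHCT alone; the sexual-risk figure cannot be checked.
- *That time to CHCT is a further competing primary.* The article already makes the 9-month comparison primary and describes the other CHCT analyses as illuminating patterns.
- *That outside-partner measures are too sparse to analyze.* The Background gives about 12% and 6% of men with multiple and concurrent partners in another area of rural KwaZulu-Natal. It also gives 32% with multiple partnerships among men aged 18 to 32 in Project Accept, which was conducted at this site. Of 245 men, that range runs from about 15 (0.06 × 245) to about 78 (0.32 × 245). Women also enter the analysis. How sparse these data will be is not known.

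**Conclusion.** The concern holds as an inconsistency in the definition of a declared primary outcome. Three sections describe it in three ways, and none names the measure, visit and model contrast that decide it. The 9-month CHCT comparison and the sample size of 350 are not affected.

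The size of the consequence is conditional. Testing all three measures at an assumed two-sided 5% would raise the false-positive chance within this outcome from 5% to between 10.9% and 14.3%, for correlations from 0.7 down to 0. The upper end is unlikely, since outside-partner acts and number of outside partners are plainly related. In the favorable direction only, the range is 5.4% to 7.3% against 2.5%. These rates show what is at stake if nothing is designated; the article does not say that it will test in this way.

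**What to change.** 1. Name one sexual-risk primary. The number of unprotected acts with the primary partner in the last 3 months is a sound candidate, for the reasons in step 1 of the working.
2. State one model contrast for it, including the visit or visits to which it refers.
3. Make the Objectives, Primary outcome: sexual behavior and Power analysis sections agree. The power section should name the partner type. If the base rate of 2.35 does not refer to the chosen measure, the detectable reduction must be recomputed.
4. Label outside-partner acts, concurrent outside partners and the proportion of acts with condom use as secondary.
5. State how alpha is handled across CHCT and this outcome, or point to where that is stated. Testing in fixed sequence after CHCT is one option. It leaves CHCT its full alpha, but sexual risk could not be claimed as confirmatory if CHCT fails.

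The cost is small: no new data and no change in the number of couples. The price is that outside-partner results are no longer confirmatory. If they must remain so, a Bonferroni split over the three measures would test each at 0.05 / 3 = 0.0167, with less power for each. With 155 couples enrolled by June 2013, the change should be a dated amendment made before anyone sees sexual-risk data by arm.

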Uthando Lwethu integrates relationship-focused education and skills training into an HIV-focused couples-based intervention. In addition, it incorporates relationship education approaches [44,60] and interdependence theory [40] to increase positive relationship dynamics. By specifically targeting relationship commitment, intimacy, and satisfaction we are directly intervening in the context of HIV risk in South Africa, that is, primary relationships. Thus, our intervention has the aim of both increasing CHCT (thus increasing mutual knowledge of serostatus), reducing sexual risk behavior for HIV with both primary and secondary partners (perhaps in the absence of knowledge of serostatus), and improving our understanding of how relationship issues influence these behavioral choices. This represents an attempt to move away from individual-level approaches, to a more integrated approach for HIV prevention.

Couples-based interventions for HIV, including those that target testing and sexual risk reduction have been identified as a high priority [11,38,63]. CHCT necessitates the testing and mutual disclosure of both partners, conditions that are essential for improving subsequent outcomes such as sexual risk reduction and improving treatment outcomes. Although interventions aimed towards improving rates of testing for male partners of antenatal clinic attendees have had similar goals, they have reported mixed results [64,65].

We will learn from our intervention whether conducting a couples-based, relationship-focused intervention is feasible in a context which presents unique challenges for couples, for example, low rates of marriage, high rates of mobility. Should the intervention demonstrate efficacy, next steps could include a rollout of this public health intervention, as well as adapting and testing our approach for couples who are experiencing current intimate partner violence, substance use, or pregnant women.

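### The second primary outcome is condom use with the primary partner in the Objectives, but three other, unranked variables in the analysis section, and nothing says which one decides the claim

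*Protocol article*

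**What the plan says.** The protocol article describes this outcome in several places.

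- **Objectives:** "A second primary outcome is reduction of sexual risk behavior (that is, condom use with primary partner in the last 3 months". This fixes one behavior, one partner type and one recall window. It gives no metric, such as a proportion of acts, consistent use or a count.
- **Data analysis, Primary outcome: CHCT:** "There are two primary outcomes for our trial: 1) participation in CHCT; and 2) sexual risk behavior". Sexual risk behavior is counted as a single outcome.
- **Data analysis, Primary outcome: sexual behavior, hypothesis 1:** "intervention participants will report fewer acts of unprotected sexual intercourse with: a) primary sex partners; and b) outside sex partners".
- **Same section, hypothesis 2:** "intervention participants will report fewer concurrent outside (that is, secondary) sex partners relative to participants in the control group".
- **Same section, on status:** "It is critical to optimize the accurate reporting of self-reported sexual risk behavior given its role as a primary outcome of our trial".
- **Power analysis:** the calculation starts from a "base rate of 2.35 unprotected sex acts per 3 months" and gives detectable means of 2.04 or 2.12 at 80% power. No partner type is attached to these figures.
- **Discussion:** the stated aim is "reducing sexual risk behavior for HIV with both primary and secondary partners", which is wider than the Objectives.

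**The concern.** A primary outcome should be a single identifiable variable, or a set with a stated rule for combining its members. Here the Objectives name one variable. The analysis section puts three under a primary heading, and none of them is expressed as condom use. The power analysis uses a wording that matches the metric of 1a and 1b but names neither partner type.

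The second primary claim is therefore open to choice. A result on unprotected acts with the primary partner, on acts with outside partners, or on number of outside partners could each be presented as the primary sexual-risk finding, with some section of the article in support. The variables are not interchangeable. Two concern different partners from the one named in the Objectives. The third may be on a different scale, because a count of unprotected acts depends on how often the couple has sex as well as on how often a condom is used.

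**Working it through.** **1. The definitions side by side**

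| Place | Behavior | Partner | Metric |
|---|---|---|---|
| Objectives | Condom use | Primary | Not stated |
| Hypothesis 1a | Unprotected intercourse | Primary | Count of acts |
| Hypothesis 1b | Unprotected intercourse | Outside | Count of acts |
| Hypothesis 2 | Concurrent partnerships | Outside | Count of partners |
| Power analysis | Unprotected sex | Not stated | Mean acts per 3 months |

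Only 1a shares both behavior and partner with the Objectives. Only 1a and 1b share the metric of the power analysis. Hypothesis 1a is the one listed variable that fits both, but no section says that it is the one.

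**2. The plan's own figures**

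- Sample size: 245 / (1 − 0.30) = 350 couples, as stated.
- Detectable means: the within-participant correlation ρ, the dispersion and the significance level are not given, so these can be matched only under assumptions. I took Poisson variance, the mean of three follow-ups, 245 individuals per arm (245 couples × 2 partners / 2 arms), two-sided 5%, 80% power and no allowance for within-couple correlation. I then solved (2.35 − m) / √[(2.35 + m) × ((1 + 2ρ)/3) / 245] = 1.96 + 0.84 for m.
  - ρ = 0 gives 2.13
  - ρ = 0.1 gives 2.11
  - ρ = 0.5 gives 2.04

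The stated 2.12 and 2.04 fit ρ of about 0.05 and 0.5. Other assumption sets could fit too. What matters here is that the powered quantity is a count of unprotected acts, not a measure of condom use.

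**3. When the metric in 1a differs from condom use**

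If condom use is read as a proportion s of acts, then unprotected acts = total acts × (1 − s). Suppose condom use rises from s0 to s1. Unprotected acts still increase if total acts grow by a factor above (1 − s0)/(1 − s1). For a 5-point rise in condom use:

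- from 30%: 0.70/0.65 = 1.077, so total acts up by more than 7.7%
- from 50%: 0.50/0.45 = 1.111, more than 11.1%
- from 70%: 0.30/0.25 = 1.200, more than 20%

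As a hypothetical example, take 4.7 acts at 50% condom use, which is 2.35 unprotected acts. With 15% more sex and 55% condom use the count is 4.7 × 1.15 × 0.45 = 2.43. Condom use has improved and the count has worsened. Only the 2.35 comes from the article; the baseline condom use and the change in frequency are assumed. This shows that the two metrics are not equivalent, and nothing about what the trial will find.

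**4. Cost of leaving the choice open**

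The article does not state the significance level for these tests; 5% two-sided is assumed. If any one of three independent tests may carry the claim:

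- either direction: 1 − 0.95³ = 1 − 0.857 = 14.3%
- favorable direction only: 1 − 0.975³ = 1 − 0.927 = 7.3%, against 2.5% for one test

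Positive correlation among the three lowers the first figure somewhat, to about 13% at a correlation of 0.4.

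**The case against.** The strongest reply is that the parenthesis in the Objectives is shorthand. Read literally, it lists condom use as a risk behavior to be reduced, which cannot be meant. The next sentence of the Objectives speaks of the frequency of sexual risk, the Abstract speaks of reductions in unprotected sex, and the power analysis uses unprotected acts over the same 3-month window. On that reading 1a is the Objectives outcome, and no conflict of metric arises for the primary partner. This reading is reasonable and supports choosing 1a. It does not settle the matter, because the article never says so, and it leaves 1b and 2 under a primary heading although they concern other partners.

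A second reply is that multiplicity rules are commonly left to a statistical analysis plan. That is fair, and the absence of such a rule is not the point. The point is that sections of the current text define the same primary outcome differently.

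Three stronger inferences are tempting and should not be drawn:

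- **That the definitions would give opposite answers in this trial.** They could, if condom use is read as a proportion. The article has no data on baseline condom use or total acts from which to say how likely that is.
- **That the intervention will probably change how often couples have sex.** It targets intimacy, commitment and satisfaction, but the article says nothing about frequency of intercourse.
- **That the trial has a 14% error rate on this outcome.** That would need a rule allowing any of the three tests to carry the claim. No such rule is stated.

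**Conclusion.** The point holds as an inconsistency in the current text. The Objectives, the sexual behavior analysis section and the power analysis do not name the same variable, and the three listed hypotheses are not ranked. Hypothesis 1a overlaps the Objectives in behavior and partner and may differ only in metric; 1b and 2 fall outside the Objectives definition.

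The consequence is a second primary claim that could be chosen among non-equivalent variables after the results are seen. Its size is a false-positive chance of up to about 14%, on the assumptions of three independent tests at two-sided 5% and freedom to rely on any one of them. The definition of the CHCT outcome is not affected.

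**What to change.** Make the Objectives, the sexual behavior analysis section and the power analysis name one variable with its partner type, metric and recall window. A natural choice is hypothesis 1a, the number of unprotected acts with the primary partner in the last 3 months: it has the partner and window of the Objectives and the metric of the power analysis. State in the power analysis whether the 2.35 base rate refers to the primary partner. Label 1b and 2 as secondary.

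Optionally, report the proportion of acts protected and the total acts with the primary partner by arm as supportive description, so that a change in condom use can be told from a change in frequency.

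The cost is rewording in three sections and in any analysis plan that follows them. The main change needs no new data. The downside is that two of the three sexual-risk hypotheses lose primary status. The choice should be fixed and dated before outcome data are compared by arm.
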